#### 4. STUDY COHORT

This study will be conducted by two investigative teams: the Joint Malaria Programme in Korogwe, Tanzania (refer to Section 4.1) and the Kenya Medical Research Institute (KEMRI) in Kilifi, Kenya (refer to Section 4.2).

**Figure 1** Map of Kenya and Tanzania indicating the principal towns in the study areas

[figure not shown]

Adapted from maps created by United Nations Dept. of Public Information, Cartographic Section.

#### **4.1. JMP Tanzania**

The Joint Malaria Programme (JMP) is a collaboration between the National Institute of Medical Research (NIMR), Kilimanjaro Christian Medical Centre (KCMC), London School of Hygiene and Tropical Medicine (LSHTM) UK, and the Centre for Medical Parasitology (CMP) in Denmark.

##### **4.1.1. JMP: Study Area Geography, Population**

Subjects will be recruited from around Korogwe division in Korogwe District. Korogwe District is one of the districts of the Tanga region of Tanzania (05°09'S, 32°28'E; area 3756 km^2). The altitude within Korogwe District varies between 300 m and 1200 m above sea level. There are three distinct climatic zones in the District: 1) a cool mountainous zone 2) wet lowlands in the south and east 3) arid lowlands in the west.

The major tribes in the District include Wasambaa, Wazigua and Wabondei as well as Waha in the town of Korogwe. The population of the Korogwe District in 2002 was 261 004; the population of Korogwe Division was 78 707.

Korogwe is connected by highway to both Dar es Salaam and Arusha/Moshi.

On average there is between 500 and 1400 mm of rain per year; 1000 to 2000 mm in the mountain zone, 800 to 1000 mm in the wet lowland zone and < 800 mm per year in the arid lowlands. There are two distinct rainy seasons, with 'short rains' from September to November and the 'long rains' from March to May. Temperatures range typically from a low of 15°C from June to August and a high of 35°C from December to March.

#### **4.1.2. JMP: Malaria Epidemiology**

The main malaria vector in the Korogwe district is *Anopheles gambiae*. *An. funestus* and *An. arabiensis* are also present in the area and responsible for some transmission. It is estimated that between 16 and 28% of people sleep under a bednet. The EIR determined in 2003 was around 90 infective bites per person, per year. Transmission of malaria tends to be highest between March and July.

#### **4.1.3. JMP: Provision of Health Care**

The EPI program offers all children BCG at birth, DTPw/HepB and Oral Polio Vaccine at 1, 2 and 3 months and Measles at 9 months *Amended 23 October 2006*.

Primary health care in the study region is provided by government run dispensaries. These typically are staffed by Clinical Officers or MCH Aid and offer outpatient treatment services.

Secondary level health care is provided by the Korogwe District Hospital. This is a district general hospital with 30 pediatric beds. The pediatric service is led by an Assistant Medical Officer. Oxygen and blood transfusion facilities are available at the District Hospital.

Referral to tertiary level facilities is rarely required, but when required will be to KCMC in Moshi. The pediatric unit has 91 beds and medical care is supervised by 7 pediatricians. Diagnostic services available include hematology, biochemistry, microbiology and radiology. In addition, there are facilities for intensive care and pediatric surgery.

#### **4.1.4. JMP: HIV and HIV services**

The prevalence of HIV in Tanzania is estimated to be approximately 9% [UNAIDS/WHO 2004a]. The prevalence among healthy children in the community is thought to be below 1%.

A Prevention of Mother to Child Transmission of HIV programme has been operational in Korogwe since 2005 and the Ministry of Health anti-viral programme is expected to reach Korogwe in the latter quarter of 2006. All patients must take part in extensive counseling before treatment. Highly Active Anti Retroviral Therapy (HAART) will be available to volunteers (if diagnosed at screening) or enrolled subjects (diagnosed during the study) with HIV *Amended 23 October 2006*

## 4.2. KEMRI, Kenya

The KEMRI/Wellcome Trust collaborative programme at Kilifi was first established in 1994. The Wellcome Trust is an independent medical research funding charity based in the UK. Its mission is to foster and promote research with the aim of improving human and animal health. One of the major priorities of the Wellcome Trust's international funding is to enhance research in developing countries, by building the capacity of local partners such as the Kenyan medical Research Institute.

### 4.2.1. KEMRI: Study Area Geography, Population

Kilifi District stretches along the Kenyan coast from Mombasa, in the South to Malindi in the North, and for 30 to 40 km inland. The District is the second poorest in Kenya. The District of Kilifi has a population of 544 000 (KEMRI's Demographic Surveillance and the Government of Kenya Census). The largest town is Kilifi, with a population of 36 000. The town is approximately 450 km SE of Nairobi, and 75 km north of Mombasa.

The local population are predominantly from the Mijikenda ethnic group. The majority are subsistence farmers. The peak rainfall is from April to August, with the peak in the malaria transmission season from mid May to September.

### 4.2.2. KEMRI: Malaria Epidemiology

The primary vector of malaria is *An. gambiae*; *An. funestus* also occurs in large numbers in the south of the district. The EIR is estimated to be up to 100 infective bites per person per year [Mbogo 2003]. Transmission of malaria tends to be highest between April and August.

Historically the use of bed nets has been low (<5%). In the last few years however partnerships between various NGOs and the Ministry of Health have enabled the distribution of large numbers of bed nets in the Kilifi District. Recent surveying has shown that among 1 to 5 year old children, bednet use has increased from 35% at the start of 2005 to 70% at the end of 2005.

Malaria is the commonest cause for children under the age of 18 months to be admitted to hospital.

### 4.2.3. KEMRI: Provision of Health Care

The EPI program offers all children BCG at birth, DTPw/Hib/HepB at 1, 2 and 3 months, Oral Polio Vaccine at 1, 2 and 3 months and Measles at 9 months ***Amended 23 October 2006.***

Primary health care in the study area is provided by a dispensary at Junju, run by the government. The dispensary operates during normal weekday working hours. A government-run health center open 7 days a week is located 14 km from Junju, in Vipingo. The center has facilities for minor surgery, obstetric care and HIV voluntary testing and counseling.

Secondary health care is provided by Kilifi District Hospital. The District Hospital has two pediatric wards; a general ward and a high dependency unit. Facilities of basic radiology, routine hematology, biochemistry and microbiology are available. Routine pediatric surgery is carried out at the District Hospital.

Referral to tertiary level facilities is rarely required, but, for example in cases requiring neurosurgery or cases of hematological malignancy, referrals are made to the government Coast General Hospital in Mombasa or the privately-run Aga Khan hospital.

*Amended 23 October 2006.*

#### **4.2.4. KEMRI: HIV and HIV services**

The prevalence of HIV in Kenya is estimated to be approximately 7% [UNAIDS/WHO 2004b]. In excess of 8% of children admitted to Kilifi District Hospital are HIV positive, but the prevalence among healthy children in the community is below 1%.

A campaign of Prevention of Mother to Child Transmission has been in operation for several years, and uptake of routine screening for HIV antenatally is about 60%. All patients must take part in extensive counseling before treatment. HAART is readily available to all HIV positive people in the community through a family clinic run by the Kenyan Ministry of Health, with staff from KEMRI. HAART is provided free of charge to patients at the clinic and CD4 counts are heavily subsidized (the charge may be waived for those who still cannot afford CD4 counts).

#### **4.3. Inclusion criteria**

*All subjects must satisfy the following criteria at study entry:*

- A male or female child of between 5 months and 17 months of age at the time of first vaccination.
- Written or oral, signed or thumb-printed and witnessed informed consent obtained from the parent(s)/guardian(s) of the child.
- Subjects who the investigator believes that their parents/guardians can and will comply with the requirements of the protocol (e.g. return for follow-up visits) should be enrolled in the study.

#### **4.4. Exclusion criteria for enrolment**

*The following criteria should be checked at the time of study entry. If any apply, the subject must not be included in the study:*

- Acute disease at the time of enrolment (acute disease is defined as the presence of a moderate or severe illness with or without fever). All vaccines can be administered to persons with a minor illness, such as diarrhea or mild upper respiratory infection without fever, i.e. axillary temperature < 37.5°C.

- Serious acute or chronic illness determined by clinical or physical examination and laboratory screening tests including, but not limited to:
  - Any confirmed or suspected immunosuppressive or immunodeficient condition, based on medical history and physical examination (no laboratory testing required).
  - A family history of congenital or hereditary immunodeficiency.
  - History of splenectomy.
  - Major congenital defects.
  - History of allergic reactions significant IgE-mediated events or anaphylaxis to previous immunizations.
  - History of any neurologic disorders or seizures.
  - Malnutrition at screening defined as weight for age Z-score less than -3 or other clinical signs of malnutrition.
- Laboratory screening tests out of acceptable limits:
  - refer to Table 9.
- Planned administration/administration of a vaccine not foreseen by the study protocol within 30 days of the first dose of vaccine(s) with the exception of tetanus toxoid or scheduled diphtheria, pertussis or measles vaccine.
- Use of any investigational or non-registered drug or vaccine within 30 days preceding the first dose of study vaccine, or planned use during the study period.
- Administration of immunoglobulins, blood transfusions or other blood products within the three months preceding the first dose of study vaccine or planned administration during the study period.
- Chronic administration (defined as more than 14 days) of immunosuppressants or other immune-modifying drugs within six months prior to the first vaccine dose (for corticosteroids, this will mean prednisone, or equivalent,  $\geq 0.5$  mg/kg/day. Inhaled and topical steroids are allowed).
- Previous participation in any other malaria vaccine trial.
- Simultaneous participation in any other clinical trial.
- Same sex twin.
- History of allergic reactions (significant IgE-mediated events) or anaphylaxis to previous immunizations.
- History of allergic disease or reactions likely to be exacerbated by any component of the vaccine.
- Any other findings that the investigator feels would increase the risk of having an adverse outcome from participation in the trial.

#### 4.5. Elimination criteria during the study

*The following criteria should be checked at each visit subsequent to the first visit. If any become applicable during the study, it will not require withdrawal of the subject from the study but may determine a subject's evaluability in the according-to-protocol (ATP) analysis.*

- Use of any investigational or non-registered drug or vaccine other than the study vaccine during the study period.
- Chronic administration (defined as more than 14 days) of immunosuppressants or other immune-modifying drugs during the study period (for corticosteroids, this will mean prednisone, or equivalent,  $\geq 0.5$  mg/kg/day. Inhaled and topical steroids are allowed).
- Administration of a vaccine not foreseen by the study protocol during the period starting from 30 days before Dose 1 and ending 30 days after Dose 3 with the exception of vaccines for DTPw, Tetanus, *Hemophilus influenzae* type B, Measles, and Polio, for which a 14 day interval around the dose of a study vaccine will be applied.
- Administration of immunoglobulins and/or any blood products during the study period.
- Failure to thrive.

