## 1. INTRODUCTION

### 1.1. Malaria

Four species of the *Plasmodium* protozoan parasite are the etiologic agents of malaria in humans (*P. falciparum*, *P. vivax*, *P. ovale* and *P. malariae*). Of these four parasites, *P. falciparum* is the major cause of severe morbidity and mortality.

There can be no doubt of the importance of *P. falciparum* malaria as a major cause of human suffering and economic drain across sub-Saharan Africa [Bremar 2001a; Gallup 2001]. In this region, it causes the deaths of between 0.5 and 2.0 million children every year and is a common reason for admission to hospital, leading each year to about 300 million clinical episodes in children under five years [Bremar 2001a].

The incidence of malaria in much of Africa is increasing for a variety of reasons: changes in agricultural practices, armed conflicts, migration of refugees, increasing drug resistance to conventional anti-malarial drugs, and insecticide resistance of the anopheline mosquito vectors. It is estimated that without effective control the number of cases of clinical malaria will more than double over the next 20 years. The burden of malaria at the country level correlates closely with the rate of economic development even after adjustment for confounding factors, indicating that malaria is an important constraint on economic progress [Bremar 2001b].

Clinical manifestations of *P. falciparum* disease appear as a result of the parasite infection of the red blood cell (RBC). Initial symptoms may include fever, chills, headache, joint and muscle pain, sweating, and vomiting. Acute complications may result from hemolysis leading to anemia and the propensity of infected RBCs to become adhesive and to be sequestered in capillaries thus causing local inflammatory reactions and damage to vital organs, leading to cerebral, hepatic, renal or pulmonary malaria. In *P. falciparum* malaria, an untreated acute attack can progress very rapidly and death may occur within a short timeframe.

Efforts to develop vaccines that target each stage of the parasite life cycle, to identify protective antigens and to understand the nature of the protective immune responses have been ongoing for the past three decades. The approach of GlaxoSmithKline (GSK) Biologicals has been to focus on vaccines that target the free sporozoite and intra-hepatic stages of the parasites (i.e. the pre-erythrocytic stages).

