Subsequently, a large safety, immunogenicity and efficacy trial in children aged 1 to 4 years from an area of high transmission was conducted in Mozambique, enrolling a total of 2022 subjects (Malaria-026 [Report, GSK data on file]; [Alonso 2004]; [Alonso 2005]). In this study, 3 doses of RTS,S/AS02A (0.25 mL dose) were administered according to a 0, 1, 2-month schedule to approximately 1000 children. The primary endpoint of this trial investigated vaccine efficacy against the onset of clinical malaria disease. Up to six months post Dose 3, the VE determined as the time to the first clinical episode (after adjustment for covariates) was 29.9% (95% CI: 11.0 to 44.8;  $p = 0.004$ ). For the entire study period, up to 18 months post Dose 3, VE for the same endpoint was 32.8% (95% CI: 20.1 to 43.4;  $p = 0.0001$ ).

The trial also offered the opportunity to investigate VE against multiple attacks of malaria and severe malaria. Against multiple attacks, VE was 27.4% (95% CI: 6.2 to 43.8;  $p = 0.014$ ) up to six months post Dose 3. For the entire study period, VE was 32.4% (95% CI: 17.6 to 44.5;  $p = 0.0001$ ). Against severe malaria, VE was 57.7% (95% CI: 16.2 to 80.6;  $p = 0.019$ ) over six months post Dose 3: for the entire study period VE was 48.6% (95% CI 12.3 to 71.0;  $p = 0.02$ ).

During the single-blind phase (Months 8½ to 21) in both Cohort 1 and 2, the proportion of children experiencing a SAE was similar in the RTS,S/AS02A and control groups

(5.1% vs. 6.8%, respectively). However, in the overall surveillance period (Months 0 to 21), there was a tendency for the proportion of children experiencing a SAE to be lower in the RTS,S/AS02A group compared to the control groups in both Cohorts 1 and 2 (20.9% vs. 28.6%, respectively). The pattern of morbidity was similar to that previously observed at the study site and described in the region. At least 97% of recipients of RTS,S/AS02A were seropositive for anti-CS antibodies and at least 97% of recipients of RTS,S/AS02A were seroprotected for anti-HBs antibodies 18 months post Dose 3 [Alonso, 2005].

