## **10.7. Study cohorts to be evaluated**

### **10.7.1. Total Vaccinated cohort**

The Total Vaccinated Cohort will include all vaccinated subjects for whom data are available. Thus, the total analysis of safety will include all subjects with at least one vaccine administration documented; the total analysis of efficacy will include all subjects with at least one vaccine administration documented and data concerning efficacy endpoint measures are available; the total analysis of immunogenicity will include vaccinated subjects for whom data concerning immunogenicity endpoint measures are available. The Total Vaccinated Cohort analysis will be performed per treatment actually administered.

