#### **10.7.4. According-to-Protocol (ATP) cohort for analysis of efficacy**

The ATP cohort for analysis of efficacy will include all evaluable subjects (i.e. those meeting all eligibility criteria, complying with the procedures defined in the protocol, with no elimination criteria during the study) for whom data concerning efficacy endpoint measures are available.

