#### **10.9.4. Calculation of time at risk**

For efficacy endpoints, the time at risk will be counted in days, and expressed as person years at risk (days/365.25).

For each subject in the Total Cohort, time at risk begins 14 days after Dose 3 for those that received Dose 3 or 2½ months after Dose 1 (Day 75) otherwise. For the According to Protocol Cohort, time at risk begins 14 days after Dose 3.

The time at risk will end whenever one of the following conditions happen first: endpoint definition met, loss of follow up, emigration from the study area, withdrawal, death, end of follow-up period.

The time at risk will take into account absences from the study area and anti-malaria drug therapy. Absences from the study area of 1 week or more will be recorded in multiples of 1 week. The date of departure will be documented. Similarly, if treatment for malaria is administered, the subject will not be considered susceptible to malaria infection for the longest duration of the combination of drugs the subject could receive for this episode as follows: 28 days if received Coartem®, 28 days if having received sulfadoxine-pyrimethamine and 7 days if having received quinine alone.

If an episode is detected during a period of time not counting for the time at risk it will not be included in the analysis, however a table will be presented showing the number of such episodes not included in the analysis.

Episodes will be included in the analysis only if the subject is identified properly showing his/her ID Card at the contact with the health facility. Only blood slides that complete the reading process according to SOP will be considered in the establishment of endpoints.

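### The ATP efficacy cohort excludes any child given a blood product during follow-up, so a child transfused for malarial anemia is removed together with the malaria episode

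*Protocol*

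**What the plan says.** Section 4.5 lists the events that can remove a child from ATP analyses. One is "Administration of immunoglobulins and/or any blood products during the study period". Another is "Failure to thrive", with no definition and no time window. The same list does limit one criterion in time: the one on unforeseen vaccines ends 30 days after Dose 3. The lead-in to 4.5 is permissive: meeting a criterion "may determine a subject's evaluability in the according-to-protocol (ATP) analysis".

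Section 10.7.4 is not permissive. Membership of the ATP efficacy cohort requires "complying with the procedures defined in the protocol, with no elimination criteria during the study".

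Section 10.9.4 sets the clock: "For the According to Protocol Cohort, time at risk begins 14 days after Dose 3". Its reasons for ending time at risk are the endpoint, loss to follow-up, emigration, withdrawal, death and end of follow-up. Meeting an elimination criterion is not among them.

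Sections 10.10.1 and 10.11.1 run every efficacy endpoint on both the ATP efficacy cohort and the Total Cohort, without ranking them. For the latter, Section 10.7.1 adds: "The Total Vaccinated Cohort analysis will be performed per treatment actually administered".

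**The concern.** An according-to-protocol cohort can reasonably be defined by what happened up to the point where endpoint counting begins. Here membership also depends on what happens afterwards, while malaria episodes are being counted, and one of the disqualifying events can be a consequence of malaria. Section 1.1 says so in general terms: "Acute complications may result from hemolysis leading to anemia". Section 4.1.3 notes that blood transfusion is available at Korogwe District Hospital. A child who meets the endpoint and is then transfused for the resulting anemia is removed because of the outcome.

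The affected cohort matters. The Glossary defines evaluable children as those included in the ATP analysis, and Section 10.6.1 sizes the trial on 400 evaluable per group. The same cohort serves the multiple-episode and hemoglobin endpoints and the annex analysis. Because the rule covers the whole study, a child whose first episode counted at Month 6½ could disappear from the annex ATP analysis after a later transfusion.

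**Working it through.** **Does the rule operate during surveillance?** Yes, on the text. Section 5.14 asks for elimination criteria to be checked at Clinic Visits 5, 6, 7 and 9. Table 3 appears to mark that check only at the vaccination visits, but its note D requires blood products to be recorded during follow-up, and Table 7 covers treatments listed as elimination criteria through to the final visit. The information needed to apply the rule is therefore collected.

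**Is only later time lost?** No. Section 10.9.4 does not censor at an elimination event and 10.7.4 works on the child, so an episode that preceded the transfusion goes too.

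**The plan's own figures (Section 10.6.1).** Attack rates are 36% and 25.2%, with 400 evaluable per group. Exact enumeration of the two-sided Fisher test at 5% gives 90.2% power (stated 90%). Expected events are 400 × 0.36 + 400 × 0.252 = 144 + 100.8 = 244.8 (stated 245). These figures reproduce; the issue is the cohort rule.

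**Baseline VE on the hazard scale**, from cumulative risks: 1 − ln(1 − 0.252)/ln(1 − 0.36) = 1 − 0.2904/0.4463 = 34.9%.

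**Sensitivity.** Let f be the share of control cases removed. The protocol gives no transfusion rate, so f = 3%, 5% and 10% are assumptions. Let r be the reduction of such removals by vaccine, also not given. The nearest figure is in Section 1.4, for the earlier RTS,S/AS02A trial: "Against severe malaria, VE was 57.7"%, with 95% CI 16.2 to 80.6.

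- Controls removed: 144f. Vaccinees removed: 144f(1 − r). Both leave the cases and the denominators.
- Control risk = (144 − 144f)/(400 − 144f). Vaccine risk = (100.8 − 144f(1 − r))/(400 − 144f(1 − r)).
- VE = 1 − ln(1 − vaccine risk)/ln(1 − control risk).

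Example, f = 10%, r = 57.7%: 14.4 controls and 14.4 × 0.423 = 6.1 vaccinees are removed. Risks are 129.6/385.6 = 0.336 and 94.7/393.9 = 0.240, so VE = 32.9%. With r = 16.2%, 12.1 vaccinees are removed, the vaccine risk is 88.7/387.9 = 0.229 and VE = 36.6%.

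| r | f = 3% | f = 5% | f = 10% |
|---|---|---|---|
| 16.2% | 35.4% | 35.7% | 36.6% |
| 30% | 35.1% | 35.1% | 35.4% |
| 57.7% | 34.4% | 34.0% | 32.9% |
| 80.6% | 33.8% | 33.0% | 30.8% |

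The change in VE switches sign at r of about 35%, which is where the reduction in removals equals the hazard-scale VE itself. That value lies well inside the 16.2 to 80.6 interval.

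**Events and power.** At r = 57.7%, f = 5% and 10% leave about 235 and 224 of the 245 events. By the pooled two-proportion approximation, power goes from 91.4% to 88.2% and 84.0%. At r = 30% (the same share of cases removed in each arm) and f = 10%, about 220 events remain and power is 89.3%.

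**The case against.** The strongest reply is that the Total Cohort is already planned for every efficacy endpoint and applies none of these criteria. A transfused child keeps the episode and the hemoglobin value there, so a comparison of the two analyses would expose any selection. That stands and limits the damage, but the ATP definition remains wrong for the cohort that the sample size refers to.

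Second, 4.5 says only that the criteria may determine evaluability, and detailed exclusion rules often sit in the report and analysis plan, which is promised and not shown. This stands in part. Section 10.7.4 as written is unconditional, however, so the two sections need to be reconciled whatever the later plan says.

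Third, the effect is probably small. Surveillance is weekly, with a rapid test for fever and treatment by the field worker, so 10% of control cases is an unsupported upper end. This stands. The final analysis also uses data only to Clinic Visit 6, which limits its exposure; the annex analyses are exposed for longer.

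Three stronger readings are tempting and are not supported:

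- A reader might infer that the rule pulls VE towards zero. That needs vaccine to reduce transfusions by more than about 35%. The 57.7% is for severe malaria rather than transfusion, comes from another formulation in children aged 1 to 4 years, and has an interval spanning the break-even point.
- A reader might treat failure to thrive as another consequence of malaria. The protocol does not state that link. What it shows is a criterion with no definition and no window.
- A reader might conclude that neither efficacy cohort preserves the randomised comparison. Analysis by vaccine actually given departs from randomisation only for a child who receives the wrong vaccine, and Sections 5.3 and 5.12 use one treatment number per child for all doses.

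**Conclusion.** The point holds as a defect in the cohort definition. Sections 4.5, 10.7.4 and 10.9.4 together remove a child transfused for malarial anemia from the ATP efficacy cohort along with the episode, which is selection on a consequence of the endpoint.

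Neither size nor direction can be fixed from the protocol. With 3% to 10% of control cases removed (assumed), VE of 34.9% moves by about 0.6 to 2.1 points downwards at r = 57.7%, and by about 0.5 to 1.7 points upwards at r = 16.2%. At the upper confidence limit and f = 10% the fall is about 4 points. These shifts rest on the assumed f and r and on the planned attack rates. No size was computed for the hemoglobin or multiple-episode endpoints. The Total Cohort analysis mitigates the problem, so this is a correction the sponsor should make because it is nearly free; it does not invalidate the efficacy assessment.

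**What to change.** In Section 10.7.4, let the elimination criteria decide ATP efficacy membership only up to the start of time at risk, 14 days after Dose 3. After that date, keep the child and all earlier episodes. If post-exposure time is a worry, censor at the date of the blood product or immune-modifying drug and add that reason to the list in 10.9.4. Apply the same time limit to failure to thrive. Reconcile the permissive wording in 4.5 with the unconditional wording in 10.7.4. Keep the full rule for the ATP immunogenicity cohort.

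In Section 10.7.1, analyse Total Cohort efficacy by randomised vaccine and reserve vaccine actually administered for safety. This matters only if a child receives the wrong vaccine.

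The cost is a few sentences and trivial programming. Data collection, sample size and the care of children are unchanged. The downside is that a few transfused children stay in the ATP efficacy cohort.
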